#### Data Safety Monitoring Board

The DSMB consists of 3 members, collectively with expertise in mental health, chronic pain, behavioral interventions, biostatistics, and clinical trials. Led by a chairperson, the DSMB’s role is to review safety data and provide recommendations about starting, continuing, modifying, or stopping the study, taking into account the following considerations: participant safety, achievement of recruitment targets, research team adherence to applicable protocol requirements, and the completeness, quality, and analysis of safety assessments. The DSMB members are independent from the study funder, trial steering committee, and research team, and they are free from conflicts of interest related to the study intervention. The DSMB met before enrollment of the first participant in the first trial and will meet before launching each subsequent trial, or more frequently if new information raises questions regarding safety.

#### Adverse Event Reporting

Study participants will be encouraged to report any real or perceived adverse events to the research coordinator through telephone or email. These instructions will be included on the study information sheet, in addition to other electronic study materials provided to participants. The coordinator will record all reported events in an adverse event log (including the participant’s name, date, and event description), which will be hosted in the study’s secure Research Electronic Data Capture (REDCap) database [68,69]. If a participant expresses thoughts of self-harm with a plan, means, and intent to carry out the plan through communication with a study team member, a member of the study team will call the participant within 1 business day with the goal of ensuring the participant has access to the appropriate crisis resources. The study coordinator will also notify one or more of the study investigators within 2 business days if an SAE is reported directly from a study participant or from someone on behalf of a participant. SAEs include death; hospitalization; suicidal or homicidal action or ideation with a plan, means, and intent to carry out the plan; new psychosis; new substance dependence; or permanently disabling event. Examples of non-SAEs include worsening anxiety or depression symptoms, newly recognized need for professional behavioral health care, and difficulty with intervention technology. Within the Wysa for Chronic Pain platform, Wysa will also track (1) crisis events that are instances when the app detects user input that is suggestive of suicidal or self-harm intent and then the user confirms this thinking on follow-up questioning by the app and (2) instances in which a user navigates to a crisis hotline from within the app. In these instances, the Wysa platform’s standard safety protocols will automatically be implemented and will direct users to national crisis hotlines.

Any serious event that is deemed by the study investigators to be attributable or possibly attributable to the study intervention will be reported to the institutional review board (IRB) within 24 business hours and to the DSMB within 5 business days of the knowledge of occurrence. In accordance with NIMH policy, any deaths or SAEs that are deemed related to study participation will also be reported to the NIMH within 5 and 10 business days, respectively. These actions and the dates of implementation will be recorded in the adverse event log. If an SAE that is attributable to the study occurs, immediate changes to the study consent form and protocol will be made if indicated. Otherwise, each quarter, the study investigators will classify any reported events as “serious” or “nonserious” and as “attributable,” “possibly attributable,” or “nonattributable” to the study intervention.

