#### Blinding

Study team members involved in outcome assessment and data analysis will not be blinded to participants’ intervention assignment because (1) the primary proximal outcomes related to immediate app engagement will be collected automatically and in real time throughout each trial and (2) the study outcomes will not be analyzed until a given trial is complete. Trial participants cannot definitively be blinded to their intervention assignment because the notification experience within Wysa for Chronic Pain will differ between the 2 intervention arms. Nevertheless, all participants will receive the same Wysa for Chronic Pain therapeutic content, participants will not explicitly be notified which study arm they are assigned to, and participants in the intervention arm with JITAIs will not necessarily be aware when a notification (or lack thereof) from Wysa for Chronic Pain is related to a JITAI under investigation.

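### The DSMB decides whether the intervention contributes to SAEs, but the only event-triggered report to it is pre-filtered by the investigators' attribution, and other events wait for a quarterly classification

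*Protocol article*

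**What the plan says.** All references are to the Protocol article.

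- **Interim Analyses.** No study outcome is analysed at interim. Stopping a trial early is considered only if the DSMB concludes that the intervention is contributing to one or more SAEs and that the risks of continuing outweigh the benefits.
- **Data Safety Monitoring Board.** A 3-member board reviews safety data, with no stated restriction to related events. It met before the first enrolment and "will meet before launching each subsequent trial, or more frequently if new information raises questions regarding safety".
- **Adverse Event Reporting, expedited route.** It covers "Any serious event that is deemed by the study investigators to be attributable or possibly attributable to the study intervention". Such an event "will be reported to the institutional review board (IRB) within 24 business hours and to the DSMB within 5 business days of the knowledge of" its occurrence.
- **Adverse Event Reporting, first step.** "The study coordinator will also notify one or more of the study investigators within 2 business days if an SAE is reported directly" by a participant or on a participant's behalf.
- **Adverse Event Reporting, everything else.** Outside the expedited route, "each quarter, the study investigators will classify any reported events as" serious or nonserious, and as attributable, possibly attributable or not.
- **Study Design and Setting; Outcomes.** The pilot lasts 4 weeks and the primary end point of each MRT is at 12 weeks.

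**The concern.** Whether the intervention contributes to SAEs is the question reserved to the independent board. The reporting rule has the research team answer it first, one event at a time, and a negative answer takes the event off the only event-triggered route to the board that the article states.

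Participants enter with a PHQ-9 or GAD-7 score of at least 10, so a hospitalization or suicidal crisis can readily be put down to the underlying illness. Both arms receive the same therapeutic content. They differ in the JITAIs, several of which pause or reduce notifications. Harm from that difference would show mainly as an imbalance between arms, which case-by-case attribution is poorly placed to reveal.

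The quarterly classification adds delay. Seriousness and attribution are the two conditions for prompt reporting. For an event not recognised at once as meeting both, the decision may come after the participant has finished. Nothing requires it to be complete before the board meets to clear the next trial.

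**Working it through.** The plan gives no figure to reproduce here, so the check compares its stated routes and time limits.

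**1. Routes by which an SAE can reach the DSMB**

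| Route | Timing | Restricted by the investigators' attribution? |
|---|---|---|
| Expedited report | 5 business days | Yes: at least possibly attributable |
| Scheduled meeting | Before each trial | No, but it falls between trials |
| Extra meeting | If new information raises safety questions | No, but the article does not say who supplies the information, or from what data |

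The first row is the only one that an individual event sets off. Under Interim Analyses, the stopping decision is needed while a trial is running.

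**2. Quarterly classification against time in the study**

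- A quarter is 52 / 4 = 13 weeks, so the longest wait is about 13 weeks. The mean wait is 13 / 2 = 6.5 weeks if events fall evenly through the quarter (assumption).
- The longest wait exceeds a participant's pilot period by 13 − 4 = 9 weeks and the MRT period by 13 − 12 = 1 week.
- As an illustration, assume that events fall evenly over the participant's period and independently of the quarter's dates. An event with r weeks of participation left is classified in time with probability r / 13. The mean of r is 2 weeks in the pilot and 6 weeks in an MRT. The share classified only after the participant has finished is then 1 − 2/13 = 11/13 ≈ 85% in the pilot and 1 − 6/13 = 7/13 ≈ 54% in an MRT. These shares apply only to events left to the quarterly route.

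**3. The two reporting clocks (minor point)**

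Let a business day have h business hours. The coordinator's limit is 2h business hours and the IRB limit is 24. If the IRB clock starts when the coordinator learns of the event, it can run out before an investigator need be told only if 2h > 24, that is, h > 12.

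| Reading of a business day | Coordinator's limit | IRB limit | Left for the investigator |
|---|---|---|---|
| h = 8 (assumed working day) | 16 | 24 | 8 business hours |
| h = 12 | 24 | 24 | 0 |
| h = 24 (24 business hours = one business day) | 48 | 24 | −24 hours |

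If the clock starts when the investigator learns of the event, there is no conflict on any reading. The DSMB limit leaves 5 − 2 = 3 business days after the latest notification, so there is no conflict there.

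**The case against.** **The filter is wide and the board has other powers.** The threshold includes events that are only possibly attributable. The board's remit is safety data in general, and a run of crises would be exactly the new information that allows an extra meeting. This stands in part. It rules out saying that the board cannot learn of unrelated-labelled SAEs during a trial. The article still states no route by which such events would come to its notice.

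**The quarterly step is residual.** SAE types are listed in advance, and a directly reported SAE reaches an investigator within 2 business days whatever its cause. This also stands in part. A reader might infer that every pilot event could be classified too late. That does not follow, because SAEs deemed related take the expedited route. Enrolment is also spread over time, so one participant's period is not the length of a trial. What remains is that an SAE not at once deemed related, or an event not at once recognised as serious, has no classification deadline shorter than a quarter.

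**Counts by arm carry little formal signal.** With 29 per arm in the pilot, 5 v 0 SAEs gives a two-sided Fisher p of 2 × C(29,5)/C(58,5) = 2 × 118,755/4,582,116 ≈ 0.052; 6 v 0 is needed to fall below 0.05. The arithmetic is right, but a safety board does not review by significance test, and the MRTs are larger.

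**Unseen documents may say more.** The full protocol, a board charter or Multimedia Appendix 1 may add detail. The article does not cite that appendix in these sections, which state specific rules, and added detail would not by itself remove the attribution condition or the quarterly default.

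**Two further inferences go too far.** A reader might conclude that the IRB deadline will lapse before an investigator hears of an event. That needs both one reading of the time unit and one starting point, and the article fixes neither. A reader might also conclude that those deciding attribution know the arm. The Blinding section says "Study team members involved in outcome assessment and data analysis will not be blinded to participants’ intervention assignment"; it does not say who decides attribution, and the listed contents of the event log do not include the arm.

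**Conclusion.** The point holds as a weakness in stated rules. The stopping decision belongs to the DSMB, yet the only event-triggered report to it depends on the investigators first deeming the SAE at least possibly attributable. Events outside that route wait up to about 13 weeks for classification, longer than a participant's 4-week or 12-week period, and classification is not tied to the pre-launch meetings.

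The conclusion rests on the routes given in the article and assumes that no unseen document sends all SAEs to the board during a trial. The number of events affected cannot be estimated, because no SAE rate is given. The averages and percentages in the working depend on the even-spread assumptions; the 13-week maximum does not.

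The clock mismatch is a matter of undefined terms. It becomes a real conflict only if 24 business hours means one business day and the clock starts with the coordinator. No finding is made about blinding of those who decide attribution.

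**What to change.** In Adverse Event Reporting:

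1. Send every SAE to the DSMB within the 5 business days already stated, whatever the investigators' attribution, with cumulative counts by arm. Give the number enrolled in each arm beside the counts, since the planned MRT arms are unequal (75 and 46, then 120 and 55).
2. Classify seriousness and attribution when an event is logged instead of each quarter, and complete all classification before each DSMB pre-launch meeting.
3. As a minor clarification, reconcile the coordinator's 2-business-day limit with the 24-business-hour IRB limit by using one time unit and stating whose knowledge starts the clock.

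Items 1 and 2 change working practice as well as wording. The cost is a few more notices to a 3-member board and somewhat more frequent review by the investigators, in trials of 58 to 175 planned participants. Item 3 is wording only. Because several trials are planned in series, the change would benefit each trial not yet launched.

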#### Protocol Modifications

Any proposed major protocol modifications will be approved by the DSMB and IRB and then communicated to relevant parties through updates to the ClinicalTrials.gov registration or direct communication with participants, as relevant.

### Dissemination Plans

Study results will be submitted for publication in peer-reviewed scientific journals and for presentation at academic conferences, as appropriate. Aggregate study results will also be shared through ClinicalTrials.gov. Furthermore, study results will inform the development of a final refined Wysa for Chronic Pain intervention, which will ultimately be available for widespread public use.

### Ethical Considerations

Participants will be recruited from the general direct-to-consumer Wysa platform, potentially as well as from other sources, such as free and publicly available online support groups and research registries (Multimedia Appendix 1). Given the minimal risk of this study, a waiver of written documentation of informed consent will be used. Instead, potential participants will receive a study information sheet that includes all elements of consent and is presented through the study institution’s secure, HIPAA-compliant, web-based REDCap system [68,69] (Multimedia Appendix 2). IRB approval for the study has been obtained by Advarra, Inc (Pro00085039). Participants will receive a US $25 electronic gift card for each time point that they complete all study questionnaires (eg, baseline, week 4, week 8, and week 12; maximum US $100 for full participation in the MRT). Participants who also complete a semistructured interview will receive an additional US $30 gift card.

## Results

This study was funded on March 4, 2024, by the NIMH as part of grant R01MH131989. IRB approval was obtained on April 11, 2025 (protocol version 1: March 26, 2025). The first participant was enrolled on June 2, 2025, and recruitment is expected to conclude in 2026.

## Discussion

### Significance and Directions for Future Research

This study is an intermediate step in the adaptation and dissemination of a digital mental health intervention that is iteratively co-designed with user input, rigorously tested, and then rapidly made available to the target population. After completion of this study, we will conduct a pragmatic, hybrid type 1 effectiveness-implementation study as the final refined version of Wysa for Chronic Pain is launched for widespread use. This process will facilitate real-world assessment of the effectiveness and reach of the intervention, and it will enable rapid, global availability of the intervention for people in need.

We anticipate that the process and results of this study will also lead to more generalizable insights. For instance, our process can serve as a reproducible, precision medicine approach to tailor digital mental health interventions for people with other medical comorbidities that frequently coexist with mental illness (eg, cancer, diabetes, stroke, heart disease, and lung disease) [70]. Additionally, we hope to identify human-centered design insights that are generalizable to other behavior-based digital health interventions for middle-aged and older adults, such as for symptom tracking, medication adherence, and medical visit reminders [71].

### Limitations

A limitation inherent in most trials involving a digital health intervention is that findings from this study will be most generalizable among people who have a base level of comfort and interest in using technology for health-related purposes. Nevertheless, especially as technology use continues to rapidly increase in this large and growing population [20], the results of this study will still be applicable to a meaningful proportion of middle-aged and older adults. For this pragmatic and somewhat formative study, results will also need to be interpreted in the context that (1) participants are permitted to receive additional treatment beyond what is delivered by the digital intervention and (2) multiple secondary outcomes are being assessed, which increases the likelihood of type 1 errors for these outcomes (but not for the singular primary outcome for each JITAI). Finally, as with most behavioral interventions, participants cannot be blinded.

### Conclusions

Completion of this mixed method series of randomized trials and semistructured interviews will result in iteratively refined JITAIs that are designed to improve usability and engagement with a digital mental health intervention by middle-aged and older adults with depression or anxiety and coexisting chronic pain. The methodological approach and the usability-related insights that are identified from this study can also be used for the development and refinement of other digital behavioral interventions for similar populations.

## Appendix

Multimedia Appendix 1 Additional study details.

Multimedia Appendix 2 Study information sheet.

## Abbreviations

BIT: Behavioral Intervention Technology
DDBT: Discover, Design/Build, and Test
DSMB: data safety monitoring board
GAD-7: Generalized Anxiety Disorder-7
HIPAA: Health Insurance Portability and Accountability Act
IRB: institutional review board
JITAI: just-in-time adaptive intervention
MRT: microrandomized trial
NIMH: National Institute of Mental Health
PHQ-9: Patient Health Questionnaire-9
PHQ-ADS: Patient Health Questionnaire Anxiety and Depression Scale
REDCap: Research Electronic Data Capture
SAE: serious adverse event
